### Assignment of interventions: allocation

#### Sequence generation {16a}

Patients will be randomised after they are included in the study, having consented, and completed the PCS (and scoring scored ≥ 24), and two preoperative appointments will be scheduled with the patients in the intervention and control groups. Patients will be randomised to either ‘CBT-CP’ or ‘PEM’ groups by using an online computer-generated block randomisation.

#### Concealment mechanism {16b}

Patient study number and group allocation will be typed onto separate pages and concealed in sequentially numbered sealed opaque envelopes.

#### Implementation {16c}

The randomisation process will be performed by an independent third party. The randomisation key/seed will also be held by an independent third party, and investigators will not have access to this key/seed until the study has been completed, except for the treating psychologist (DL) assigned to this trial. DL will allocate patients to either study intervention only after opening the sealed envelopes prospectively as participants are enrolled. DL will not have any additional involvement in data collection or analysis.

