### Who will take informed consent? {26a}

The senior pain psychologist (DL) delivering the perioperative interventions for this trial will screen for potential trial participants, after breast cancer surgery clinic nurses identify potential candidates for the study. Patients that meet the eligibility criteria will be contacted, and informed consent will be obtained. All potential participants will have the opportunity to withdraw at any time point during the study period.

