### Strategies to improve adherence to interventions {11c}

All participants for this trial will receive a total of four psychological based interventions (see the ‘Intervention description {11a}’ section). Each intervention session lasts for 60 min. To ensure patient adherence to the study interventions during the trial period, all participants will be well-informed during the consent process. The study participation burden, such as duration and timing of each psychology session, and completion of primary outcome questionnaires at 1 and 3 months post-surgery will be explained. The senior pain psychologist responsible for screening potential study participants will record all eligible candidates and those that do not proceed with the study due to ineligibility, non-consent, or withdrawal. In so far as it is possible, only eligible and fully willing individuals will proceed to randomisation and allocation of the patient to either the CBT-CP or PEM group.

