#### Plans to promote participant retention and complete follow-up {18b}

During the screening process, potential participants will receive an extensive patient information leaflet about the study. The senior pain psychologist involved in this study will emphasise the importance of patient participation and the expectation to complete the study interventions and the various follow-up questionnaires at the time of screening and enrolment to optimise retention and meaningful data collection.

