
Our study methods endeavour to prevent bias where possible via randomisation, concealment of allocation, specified procedures and efforts to reduce incomplete data, use of a statistically appropriate sample size and consistent thorough follow-up of study patients. The study results will contribute to current evidence in surgical pain treatment and management and inform current treatment practices and standards.

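### The randomisation section exempts the unblinded psychologist who screens candidates from the ban on access to the key/seed, which contradicts the claimed allocation concealment

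*Protocol article*

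**What the plan says.** **Key and envelopes.** Concealment mechanism {16b} relies on opaque, sealed envelopes numbered in order. Implementation {16c} states "The randomisation key/seed will also be held by an independent third party", and then that "investigators will not have access to this key/seed until the study has been completed, except for the treating psychologist". The next sentence has the psychologist allocate each patient only on opening the envelopes prospectively, as patients are enrolled. The section ends by keeping this person out of all other data collection and analysis.

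**Screening and consent.** Under Who will take informed consent? {26a}, the senior psychologist "delivering the perioperative interventions for this trial will screen for potential trial participants", after clinic nurses have put candidates forward. The section continues: "Patients that meet the eligibility criteria will be contacted, and informed consent will be obtained". No other person is named there as taking consent.

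**Eligibility records and enrolment.** Strategies to improve adherence {11c} says: "The senior pain psychologist responsible for screening potential study participants will record all eligible candidates", together with those who do not go forward and the reason. Under {18b}, the same psychologist stresses to patients the importance of completing the sessions and the "various follow-up questionnaires at the time of screening and enrolment".

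**Blinding.** {17a} states that the psychologist is not blinded, because this person delivers both programmes.

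**The claim made.** The Discussion says: "Our study methods endeavour to prevent bias where possible via randomisation, concealment of allocation".

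**The concern.** Allocation concealment means that whoever decides whether and when a patient enters the trial cannot know the next assignment. {16c} lifts the restriction on the list for one investigator only, and that investigator is the screener.

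There is room for judgement at that step. Eligibility criteria {10}, repeated in Sample size {14}, exclude patients whose non-compliance is merely suspected. A screener who can see the next allocation could, even without meaning to, apply that criterion more or less strictly according to the arm coming up. The groups would then differ in motivation or expected adherence before treatment starts, in a small trial with a patient-reported primary outcome. The planned mixed model is said to account for baseline scores, so an imbalance in baseline pain would be partly addressed. Selection on unmeasured traits would not.

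**Working it through.** The point is procedural. No figure in the plan measures it, so the check is to set the statements side by side.

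**1. The sample size is not affected.** Inputs from Sample size {14}: difference 2, SD 2.3, type I error 0.05 (two-sided, from {20a}), power 80%. Then n per arm = 2 × (1.960 + 0.842)² × 2.3² / 2² = 2 × 7.85 × 5.29 / 4 = 20.8, so 21. With 10% dropout, 21 / 0.9 = 23.3, so 24 per arm and 48 in total. The plan's figures reproduce, and nothing below changes them.

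**2. Who does what before allocation.**

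| Step | Person | Section |
|---|---|---|
| Identify candidates | Clinic nurses | {26a} |
| Screen | Treating psychologist | {26a}, {11c} |
| Administer PCS | Team member, not named | {15} |
| Obtain consent | Passive wording; only the psychologist is named in the section | {26a} |
| Record eligible and excluded patients | Treating psychologist | {11c} |
| Hold key/seed | Independent third party | {16c} |
| Permitted access to key/seed before study end | Treating psychologist, sole exception among investigators | {16c} |
| Open envelopes and allocate | Treating psychologist | {16c} |
| Deliver both therapies, unblinded | Treating psychologist | {11a}, {17a} |

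**3. Do the statements fit together?** The envelope procedure works only if the person opening the envelopes cannot learn their contents by another route. The exception in {16c} opens that route for exactly that person. The two rules cannot both serve concealment. With list access, sequential opening protects nothing. Without list access, the exception has no function.

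**4. Extent.** The exception is not limited in time or to allocations already made. Read literally, it covers all 48 assignments. Trial status reports 37.5% recruited at the time of writing, that is 0.375 × 48 = 18 patients.

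**5. What the order of events already protects.** Sequence generation {16a} puts randomisation after inclusion, consent and a qualifying PCS score. Table 2 puts the PCS in the enrolment column, but the baseline BPI in the allocation column. The article does not say that these records are locked before an envelope is opened.

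**The case against.** The strongest reply is that the exception is loose drafting. The authors may have meant only that the psychologist, unlike the other investigators, learns allocations before the study ends, because this person must deliver the therapy. The third-party custody of the key and the prospective opening of envelopes support that reading. It is plausible, and a reader who infers from {16c} that the psychologist knew the allocations in advance goes further than the document does. What remains is that {16c} deals with envelope opening in its own sentence and grants the exception to the key/seed itself. If the milder meaning was intended, the text still has to be corrected.

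Other replies also stand in part:

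- Consent is worded passively and an unnamed team member gives the PCS, whose cut-off is objective. That the psychologist takes consent is a fair inference from the heading of {26a} and from {18b}, but it is not stated. The screening and eligibility-recording roles are stated.
- A reader might treat the phrase "only eligible and fully willing individuals will proceed to randomisation" as a further discretionary exclusion. It describes consent. The judgement-based criterion relied on here is suspected non-compliance.
- A reader might argue that a blocked list at a single centre is predictable to an unblinded enroller even without the key. That depends on the block size, on whether it is fixed, and on whether the psychologist knows it. The article gives none of these and may properly leave them to the full protocol, so no figure for predictability is supportable.
- The therapist has to be unblinded. That is true after allocation, but it does not require access to the list beforehand.
- The psychologist is kept out of other data collection and analysis. That limits bias in outcome assessment, but not selection at entry.

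**Conclusion.** The concern holds as a contradiction in the stated procedure. {16c} permits the screener to know upcoming allocations, which undercuts the envelope mechanism in {16b} and {16c} and the claim of concealment in the Discussion. Its reach on the literal text is all 48 allocations. The conclusion rests on two things: reading the exception as applying to the key/seed, which is what the sentence says, and the psychologist's screening role, which {26a} and {11c} state outright.

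Two things are not established: that foreknowledge occurred, and how far the 3-month pain comparison would move if it had. The document contains nothing from which such a shift could be calculated. The point still deserves correction, because the remedy is cheap and selection on unmeasured traits could not be removed in the analysis.

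**What to change.** - In {16c}, delete the exception for the treating psychologist, so that this person learns each allocation only when it is released.
- State that the independent third party already in the trial keeps both the key/seed and the envelopes. It releases one allocation at a time, after eligibility (including the judgement on suspected non-compliance), consent, PCS and baseline BPI have been recorded and locked.
- In the trial report, give the number of patients allocated under the arrangement now described, and say whether the psychologist in fact had access to the list.

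The existing sequence can stay in use. The cost is a short amendment, a release step by phone or email, and a brief delay between enrolment and allocation. Sample size and analysis are unchanged.

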### Assignment of interventions: blinding

#### Who will be blinded {17a}

The treating psychologist will not be blinded as he is required to deliver both interventions associated with this trial. All other members of the research team involved in data collection and analysis will be blinded to the group allocation. In addition, patients will also be blinded because they will not be informed if they are receiving CBT or PEM other than that they are receiving one of two types of psychological interventions.

#### Procedure for unblinding if needed {17b}

Unblinding of trial participants to fellow research team members will occur only after creation of a final locked analysis dataset when the last patient has provided data at 3-month follow-up and after data has been statistically analysed by (MBC and DB).

### Data collection and management

#### Plans for assessment and collection of outcomes {18a}

There will be three time points in which data collection will occur (preoperative, intraoperative, and postoperative). Data will be obtained from electronic and paper patient records. In addition, various questionnaires will be used to gather data to assess for the primary and secondary outcomes outlined for this trial (see the ‘Outcomes {12}’ section).

#### Plans to promote participant retention and complete follow-up {18b}

During the screening process, potential participants will receive an extensive patient information leaflet about the study. The senior pain psychologist involved in this study will emphasise the importance of patient participation and the expectation to complete the study interventions and the various follow-up questionnaires at the time of screening and enrolment to optimise retention and meaningful data collection.

### Data management {19}

All data will be recorded on a study specific case report form (CRF) that has the patient’s unique study identifier code on each page. Study investigators will enter the data from CRF’s into a designed study specific REDCap database that is password protected. Data will be entered primarily by one study investigator (AM) and verified by a different study investigator (CE) to minimise data entry errors (e.g., incorrect, or duplicate data). Both researchers will be blinded to group allocation.

The data collected and all the research-related documents (both hard copies and electronic copies) will be stored securely in a locked office in the principal investigator’s office at the Mater Misericordiae University Hospital (MMUH). Only the principal investigator and the co-investigators can have access to these documents. The records will be kept for 5 years following study closure. All electronic files will be encrypted and accessed via password protected computers.

The electronic REDCap database also allows for specified ranges and automatic calculations to reduce entry errors. The study REDCap database will have automatic calculations for study questionnaires and specified ranges entered for each questionnaire response to ensure accurate data entry. Data will be cleaned by investigators upon completion of data collection to ensure good quality data.

### Confidentiality {27}

All the data collected will remain anonymous and confidential. A unique subject number will be provided to each individual patient participating in the study. The front page of the CRF which will be labelled with both the randomisation number and patient information will be stored separately to the remainder of the CRF containing data about the patient to ensure data is re-identifiable. Only study investigators will have access to the data as CRF forms will be stored in a locked office that only study investigators have access to.

### Plans for collection, laboratory evaluation and storage of biological specimens for genetic or molecular analysis in this trial/future use {33}

Not applicable, no samples will be collected.

### Statistical methods

#### Statistical methods for primary and secondary outcomes {20a}

Outcome analyses will be conducted by researchers (MBC and DB) who will be blinded to treatment group allocation. Descriptive statistics will be calculated for all outcome measures at each time point, including for continuous variables: means, standard deviations or medians with ranges of scores, and for categorical variables: frequencies and percentages.

Descriptive and inferential statistics will be obtained using the appropriate statistical methods required to address the study objectives. The primary analysis will compare the effect of the interventions on the primary outcomes; average pain severity at 3 months post-surgery. Outcome analyses will be conducted according to an intention to treat principle, i.e. all randomised participants will be included in the main analysis and will be analysed as randomised, regardless of protocol adherence. Secondary analysis will involve the analysis of the secondary outcomes: QoR-15 at 24 h post-surgery, PCS, HADS and average pain interference on the BPI short form at 3 months post-surgery. Linear mixed models on the outcome measures over time will be fitted to evaluate the effectiveness of both interventions, which intrinsically adjusts for baseline scores. Statistical significance will be assessed from a *p*-value < 0.05 from the group by time interaction term. For all tests, 2-sided *p*-values will be used, which will be reported to 4 decimal places with *p*-values less than 0.001 reported as *p*< 0.001. In the case of a significant result, contrasts of the group effects at each assessment time point will be used to investigate the direction and pattern of effects. Irrespective of statistical significance, the mean changes and confidence intervals will be reported. An up-to-date version of SPSS will be used to conduct analyses.

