### Outcomes {12}

Primary outcome:
Brief Pain Inventory Short form: average pain severity score. [time frame: 3 months postoperative]
Brief Pain Inventory (BPI) short form will be used to assess for CPSP after breast cancer surgery. This assessment will be conducted by a member of the research team. The BPI assesses for quality of life and pain, and its scale is measured between 0 and 10, where ‘0’ indicates no pain and ‘10’ indicates severe pain. A decrease in the BPI score of 2 or more from the baseline score is considered clinically significant and indicates an improvement in severity of the patient’s cancer and or non-cancer pain [18]

Secondary outcomes:

Secondary outcomes of the study include pain interference, quality of recovery from surgery, levels of pain catastrophising, reported depressed mood and levels of anxiety. These will be measured as follows:
Brief Pain Inventory Short form: average pain interference score. [time frame: 3 months postoperative]
i.BPI average pain interference score assess for interference the pain has on the patient’s functioning. BPI is measured between 0 and 10, where ‘0’ indicates no interference and ‘10’ indicates severe interference with quality of life [18].Quality of Recovery-15 (QoR-15) [time frame: 24–48 h, post-operative]
QoR-15 is a 15-item questionnaire which is used as a tool to assess overall patient recovery and pain after surgery. Participant will be asked to complete this questionnaire within 24–48 h after their surgery. It is scored between 0 and 150, where the greater the number indicates excellent post-operative recovery [19].Pain Catastrophising Scale (PCS). [time frame: 1 and 3 months, post-operative]
PCS is a 13-item questionnaire designed to measure levels of pain-catastrophizing. The scale comprises 13 items which yield an overall catastrophising score, which is a composite of magnification, rumination and helplessness subscales. An overall score of greater than 24 is significant for pain catastrophising [10, 13, 20]Hospital Anxiety and Depression Scale (HADS). [time frame: 1 and 3 months, post-operative]
HADS is a 14-item self-report questionnaire that was developed and found to be a reliable for detecting states of depression and anxiety in hospital patients, including those with cancer. A depression or anxiety score of greater than 10 is considered significant [21]

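### The single significance rule (group-by-time interaction) does not fit two secondary outcomes: for HADS, which has no scheduled baseline, it misses a benefit held equally at 1 and 3 months, and for QoR-15, measured once, the term does not exist

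*Protocol article*

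**What the plan says.** Section {20a} of the protocol article lists the secondary outcomes ("Secondary analysis will involve the analysis of the secondary outcomes: QoR-15 at 24 h post-surgery, PCS, HADS and average pain interference", the last at 3 months) and then gives one method: "Linear mixed models on the outcome measures over time will be fitted to evaluate the effectiveness of both interventions, which intrinsically adjusts for baseline scores". The decision rule follows, with no exception for any outcome: "Statistical significance will be assessed from a *p*-value < 0.05 from the group by time interaction term". Comparisons at individual visits are conditional on that test: "In the case of a significant result, contrasts of the group effects at each assessment time point will be used". One safeguard is unconditional: "Irrespective of statistical significance, the mean changes and confidence intervals will be reported".

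The assessment schedule is in Outcomes {12} and Table 2:

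- **HADS.** {12} gives "Hospital Anxiety and Depression Scale (HADS). [time frame: 1 and 3 months, post-operative". Table 2 marks 30 and 90 days only, with nothing at enrolment or allocation.
- **QoR-15.** {12} gives "Quality of Recovery-15 (QoR-15) [time frame: 24–48 h, post-operative". Table 2 marks a single assessment, at 24–48 h. Section {20a} puts it at 24 h.
- **BPI.** Table 2 marks allocation, 30 days and 90 days.
- **PCS.** Table 2 marks enrolment, 30 days and 90 days.

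**The concern.** A group-by-time interaction measures a treatment effect when one of the times precedes treatment: the arms start level and then separate. BPI and PCS have such a time point. HADS, by Table 2, does not. Table 1 places the last therapy session 1–2 weeks after surgery, so both HADS visits come after treatment has ended. The interaction then asks only whether the arm difference at 3 months departs from that at 1 month, and an effect already present at 1 month and maintained cancels out.

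Depression, anxiety and quality of recovery are all named among the secondary objectives {7}. Under the rule as written, a lasting HADS benefit would usually be reported as non-significant, and the visit-level contrasts that could show it would not be opened. A significant result could also arise because a benefit is shrinking. For QoR-15, the p-value that the rule calls for cannot be computed.

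**Working it through.** **1. The plan's own figure.** Inputs from Sample size {14}: difference 2, SD 2.3, alpha 0.05 (two-sided by {20a}), power 80%.

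n per arm = 2 × (1.960 + 0.842)² × 2.3² / 2² = 20.8, rounded up to 21. Allowing for 10% dropout, 21 / 0.9 = 23.3, rounded up to 24. Both figures reproduce. The point does not depend on them; they supply only the illustrative n and effect size below.

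**2. What the HADS interaction tests.** Let δ1 and δ3 be the differences between arms at 1 and 3 months. With two visits and complete data, the interaction test is a two-sample t-test on the change from 1 to 3 months. Its expected value is δ3 − δ1, and the SD of the change is SD × √(2(1 − ρ)), where ρ is the correlation between visits. If δ1 = δ3, the expected value is zero whatever the size of the benefit. The rejection rate is then alpha, 5%. This step needs no assumption about effect size or correlation.

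**3. Illustration.** The protocol gives no HADS effect, SD or correlation. Assumed: a standardised effect of 2/2.3 = 0.87, borrowed from the BPI inputs; 21 per arm; ρ from 0.3 to 0.7. The direct 3-month comparison has noncentrality 0.87 / √(2/21) = 2.82 on 40 degrees of freedom, which gives power 0.785. Simulation (20,000 trials per correlation) gave 0.783 to 0.789.

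| True HADS benefit (SD units) | Test | ρ = 0.3 | ρ = 0.5 | ρ = 0.7 |
|---|---|---|---|---|
| 0.87 at both visits | interaction (stated rule) | 0.049 | 0.051 | 0.049 |
| 0.87 at both visits | 3-month difference | 0.78 | 0.78 | 0.79 |
| 0.87 at both visits | group effect averaged over visits | 0.93 | 0.89 | 0.85 |
| half at 1 month, full at 3 | interaction | 0.21 | 0.28 | 0.43 |
| none at 1 month, full at 3 | interaction | 0.64 | 0.79 | 0.94 |
| 0.87 at 1 month fading to 0.5 at 3 | interaction | 0.17 | 0.22 | 0.33 |

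The last row shows rejections that occur because the effect is shrinking.

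**4. Why the baseline matters.** With a baseline visit added (three visits, equal correlations, the same 0.87 SD at both follow-ups), the interaction detects the sustained benefit with simulated power 0.66, 0.83 and 0.97 at ρ = 0.3, 0.5 and 0.7. The rule can therefore pick up a sustained benefit on the BPI and PCS schedule. The missing first assessment is what defeats it for HADS.

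**5. QoR-15.** One assessment means there is no time factor, no interaction and no baseline. The statement that the model "which intrinsically adjusts for baseline scores" does not hold for QoR-15, nor for HADS as scheduled.

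**The case against.** **The HADS interaction is a usable test.** This stands in part. A reader might infer that the plan cannot evaluate HADS at all. It can: the term is estimable and responds to growing or fading effects, with the power shown in the table. The defect is limited to a benefit held steady. Nor does the protocol say which time course is most likely, so it does not support calling the sustained pattern the most plausible one.

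**QoR-15 would get an ordinary two-group test.** Probably so in practice. The phrase about outcome measures over time can be read as covering repeated measures only, and {20a} promises appropriate methods in general terms. An article may leave the name of that test to a fuller document. A wrong QoR-15 analysis is therefore unlikely. What remains is a rule worded as if it covered an outcome to which it cannot apply.

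**The blank HADS cell may be a slip in Table 2.** Possible. The {12} time frame does not settle it, because PCS has the same one there and does have a baseline in Table 2. But nothing in the article schedules a baseline HADS, and if one exists the table needs correcting.

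**Other reporting limits the harm.** Descriptive statistics at each time point would let a reader see the HADS differences by visit, but they provide no test. The mean changes reported regardless of significance do not help: without a baseline, the only HADS change is from 1 to 3 months, and QoR-15 has none.

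**Missing data.** A reader might add that the mixed model cannot keep every randomised patient in the QoR-15 analysis. That is true of any analysis of a single assessment without imputation, including the one recommended here, so it is not a fault particular to this plan.

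**Conclusion.** The concern holds for HADS as scheduled. The stated significance test has zero expected signal for a benefit held equally at 1 and 3 months, so it rejects about 5% of the time whatever the size of that benefit. That result is algebraic and rests only on Table 2 being right that HADS has no baseline. The comparison figure of about 79% power for a direct 3-month contrast is an illustration: it rests on an effect of 0.87 SD carried over from BPI and 21 per arm, and it would change with the true HADS effect and SD.

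For QoR-15 the finding is one of wording: the rule should not be written as covering it.

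This should be corrected, but it does not threaten the trial's main conclusion. Section {20b} bases superiority on the primary intention-to-treat analysis, and BPI has a baseline, so this defect does not reach the primary outcome.

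**What to change.** In {20a}:

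1. Test HADS-anxiety and HADS-depression by the between-group difference at 3 months from the mixed model, with the 1-month difference also reported, and not by the interaction.
2. Analyse QoR-15 as a single between-group mean difference with a 95% CI.
3. Limit the statement about baseline adjustment to BPI and PCS.
4. Give QoR-15 the same time in {20a} (now 24 h) as in {12} and Table 2 (24–48 h).

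If a baseline HADS is in fact collected, correct Table 2 and adjust for it. If not, adding one for patients still to be enrolled is optional. Randomisation makes the 3-month comparison valid without it, and a baseline only improves precision. At the recruitment reported under Trial status (37.5% of 48, which is 18 patients), 30 patients could still provide one, at the price of one 14-item questionnaire each.

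The essential changes cost only wording, with no extra patients or visits. They should be made before unblinding, so that the choice of test cannot be influenced by the results.

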### Sample size {14}

The primary outcome is the difference in the BPI average pain severity score between the study groups, three months after surgery. A clinically important difference on the BPI is 2 raw score reduction on the 11-point Numerical Pain Rating Scale (NRS) [22–24]. The standard deviation (SD) of BPI scores after breast surgery is in the order of 2.3 [25] on this scale. Taking a BPI score reduction of 2 as the minimal clinically relevant difference, then *n* = 21 patients would be required each arm if type I error = 0.05 and type II error is 0.2 (power 80%). This calculation was verified by using an online power calculator (https://www.sealedenvelope.com/power/continuous-superiority/). The screening process for potential eligible participants will be a very thorough methodological process. As mentioned in the exclusion criteria, any suspected non-compliant participants will not be enrolled or randomised to either of the study’s intervention. By taking this approach, we endeavour to limit the number of dropouts to approximately 10%, and therefore, we propose to enrol 24 eligible patients in each group (*N* = 48 total).

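### The group-by-time interaction is not the baseline-adjusted 3-month comparison that the protocol takes it to be, and the stated 80% power was not calculated for it

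*Protocol article*

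**What the plan says.** Sample size {14} defines the quantity of interest as the "difference in the BPI average pain severity score between the study groups, three months after surgery". The target is set by "Taking a BPI score reduction of 2 as the minimal clinically relevant difference", and the spread by "The standard deviation (SD) of BPI scores after breast surgery is in the order of 2.3". With type I error 0.05 and 80% power this gives 21 per arm. After an allowance of about 10% for dropout, "we propose to enrol 24 eligible patients in each group". No baseline SD, SD of change or baseline-to-follow-up correlation appears.

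Statistical methods {20a} names average pain severity at 3 months as the primary comparison. It then fits linear mixed models to the outcome measures over time, "to evaluate the effectiveness of both interventions, which intrinsically adjusts for baseline scores". Significance is read from the group-by-time interaction at p < 0.05 ("For all tests, 2-sided" p-values). Contrasts at each visit are used to look at direction and pattern only after a significant result.

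Table 2 under Participant timeline {13} schedules BPI at allocation, 30 days and 90 days.

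**The concern.** A mixed model does not adjust for baseline merely by being a mixed model. It does so if baseline is a covariate, or if baseline is a response and the arms share one baseline mean. The article states neither.

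If baseline is an ordinary response with separate arm means, the interaction compares changes from baseline. If only the 1- and 3-month scores are responses and there is no covariate, baseline does not enter at all. The quoted sentence is inaccurate on both readings.

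Two things are at stake. First, the 80% power belongs to a different test from the one that decides the trial, because the per-visit contrasts come into play only after a significant interaction. Second, a chance baseline difference between arms carries over in part into a comparison of changes, although the baseline BPI needed to remove it is already collected.

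**Working it through.** **Inputs from the protocol.** Difference 2, SD of post-surgery scores 2.3, alpha 0.05 two-sided, power 80%, 21 evaluable and 24 enrolled per arm; BPI at allocation, 30 and 90 days.

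**Assumptions, not in the protocol.** Correlation rho between baseline and 3-month BPI; baseline SD s0; for the 2-df test, compound symmetry and the size of the 1-month effect.

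**1. The plan's own figure.** n = 2 × 2.3² × (1.960 + 0.842)² / 2² = 2 × 5.29 × 7.849 / 4 = 20.76, so 21 per arm; 21 / 0.9 = 23.3, so 24. Both figures reproduce, for a plain 3-month comparison of two means. Power at 21 per arm is 80.4% by the normal approximation and 78.5% by the t distribution.

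**2. The 3-month component of the interaction.** With baseline as a response and free arm means, this is the difference in mean change. The SD of change is √(s0² + 2.3² − 2·rho·s0·2.3), which is 2.3·√(2(1 − rho)) when s0 = 2.3. The standard error is that SD × √(2/21). For example, at rho 0.3 and s0 = 2.3 the SD is 2.721, the standard error is 2.721 × 0.3086 = 0.840, and the noncentrality is 2 / 0.840 = 2.38.

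**3. The baseline-adjusted 3-month contrast.** The residual SD is 2.3·√(1 − rho²), on 39 df.

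Power with 21 per arm, noncentral t:

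| rho | Change, s0 = 2.3 | Change, s0 = 1.6 | Change, s0 = 1.2 | Baseline-adjusted |
|---|---|---|---|---|
| 0 | 49% | 62% | 68% | 78.5% |
| 0.2 | 59% | 71% | 76% | 80% |
| 0.3 | 64% | 76% | 80% | 82% |
| 0.5 | 79% | 87% | 89% | 89% |
| 0.6 | 87% | 93% | 93% | 93% |

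The change variance equals the planned variance when rho = s0 / (2 × 2.3). That is 0.50 for s0 = 2.3, 0.35 for 1.6 and 0.26 for 1.2. Below this value the change contrast is weaker than planned, and above it stronger. On the normal approximation with s0 = 2.3, 80% power needs rho of about 0.495 with 21 per arm, or 0.42 if all 24 per arm are evaluable.

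**4. The declared test.** Three visits give the interaction 2 df. Take equal SDs, compound symmetry, a 2-point effect at 3 months and a 1-point effect at 1 month. The noncentrality is then 21 / (5.29 × (1 − rho)), which is 4.96, 5.67 and 7.94 at rho 0.2, 0.3 and 0.5. Power (chi-square, 2 df) is 50%, 56% and 71%. If the 1-month effect is 0 or 2 points, power is 63%, 69% and 84%.

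**5. Baseline imbalance.** With equal SDs, an observed baseline difference d shifts the expected difference in change by −(1 − rho)d. The standard error of d with 24 per arm is 2.3 × √(2/24) = 0.66 points, or 0.35 if the baseline SD is 1.2.

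**The case against.** A reader might infer that the trial is underpowered, or that the tested quantity simply has a larger variance than planned. The document does not support that:

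- No correlation or baseline SD is given. Above the break-even correlation the change contrast has more power than planned.
- A low correlation cannot be taken for granted. Background and rationale {6a} lists chronic pre-operative pain among the most important predictors of chronic post-surgical pain. This does not fix rho, but it points away from a very low value.
- A threshold of 0.5 requires the baseline SD to equal the post-surgery SD. It falls if pain varies less before surgery.
- The 3-month change contrast is only one component of the declared 2-df test, so its power is not the power of that test.
- A reader might also think that a baseline imbalance passes in full into the change comparison. With equal SDs only the fraction (1 − rho) does.

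A further defence is that a constrained-baseline model would make the interaction terms the baseline-adjusted effects, and that such parametrisation is usually left to an analysis plan, which is not at hand. The first part is true of that model. But the article does more than leave the detail open: it says the adjustment follows from the model itself and ties the decision to the interaction. Even under the constraint, the joint interaction would remain a different test from the 3-month comparison that was sized. These objections limit the size of the point but do not answer it.

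**Conclusion.** The point holds as a mismatch between the analysis and the sample size. As described, the interaction is a joint 2-df comparison of changes from baseline, the statement that baseline is adjusted for is not accurate for that model, and the 80% power was calculated for a plain 3-month comparison.

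A power shortfall is possible but not shown. With 21 per arm and a baseline SD of 2.3, the 3-month change contrast ranges from 59% power at rho 0.2 to 87% at rho 0.6. With a baseline SD of 1.2 to 1.6 it has 71% to 76% at rho 0.2 and 76% to 80% at rho 0.3. The 2-df test can be lower still, depending on the 1-month effect.

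The recommendation does not depend on the unknown figures. Within the stated SD and difference, the adjusted contrast keeps about 80% power or more whatever the correlation, and its residual variance is never larger than the variance of change.

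**What to change.** Name the between-group difference in BPI average pain severity at 3 months, adjusted for baseline, as the primary test. Take it from one of two models:

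- a mixed model of the 1- and 3-month scores with baseline BPI and its interaction with visit as covariates; or
- a mixed model with baseline as a response and a common baseline mean across arms.

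The covariate version drops anyone without a baseline BPI unless that value is handled. The common-mean version keeps them, which fits the commitment in {20a} to include all randomised participants.

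Handle pain interference and PCS in the same way, since Table 2 provides a baseline for both. Replace the sentence on intrinsic adjustment with this specification. In Sample size {14}, tie the stated power to this contrast: with 21 evaluable per arm, 78.5% by the t distribution at rho 0, rising with rho.

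No new data or patients are needed. The cost is a wording amendment with ethics approval, as {25} requires. The article reports 37.5% recruited, and {17b} keeps allocation blinded until after the analysis, so the change can be made before unblinding.
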